#### 11.4.3 Secondary endpoint analysis

Statistical analysis of secondary objectives, especially between control and treatment arm will be performed according the nature of the outcome parameter. Nominal and dichotomous, outcomes will be compared by Chi-squared or Fisher's exact tests, continuous variables will be compared by T-tests (after  $\log_2$  transformation) or by Mann-Whitney-U tests and censored survival outcomes by Cox-regression analysis. Potential confounders will be considered in corresponding statistical models. Multiple testing will be corrected for by the Holm's Step-Down method or by the false discovery rate (FDR) method after Benjamini-Hochberg (especially omics data) [42]. Adjusted p-values (q-values) below 0.05 will be considered as statistically significant.

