### 8.7.5 Tumor biopsies

Additional biobanking will be done from pretherapeutic biopsies (day -21 to -1), which are collected anyhow for routing clinical diagnostic, as well as from tumor resected specimen (between week 15 to 17). Additional study specific interventions would include tumor biopsies on day 14 and 28. Tissue biobanking material will be used for genomic, transcriptomic, epigenomic and/or proteomic investigations/correlations with therapy response and clinical outcome.

Genomic analysis of circulating tumor DNA (ctDNA) and tumor tissue DNA will include standard high throughput next generation sequencing (NGS) technologies, such as whole genome sequencing (WGS) and/or whole exome sequencing (WES).

Transcriptomic analysis will include standard high-throughput technologies, such as single-cell RNA sequencing (scRNA-seq), single-cell T-cell receptor sequencing (scTCR-seq), single-cell B-cell receptor sequencing (scBCR-seq), single nuclei RNA sequencing (snRNA-seq), spatial transcriptomics (Visium Spatial platform, 10X Genomics), cellular indexing of transcriptomes and epitopes by sequencing (CITE-seq) [35] and/or RNA expression and protein sequencing assay (REAP-seq) [36].

Epigenomic analysis will include reduced representation bisulfite sequencing (RRBS) [37] and/or chromatin immunoprecipitation DNA-sequencing (ChIP-seq) [38]–[40].

Proteomic and metabolomic will include standard high-throughput technologies, such as orbitrap mass spectrometry, matrix assisted laser desorption/ionization (MALDI), electrospray ionization (ESI), liquid chromatography–mass spectrometry (LC–MS), gas chromatography–mass spectrometry (GC–MS) and/or cytometry by time of flight (CyTOF) [41]. Protein analysis of single cell suspensions will include standardized flow cytometry (FCM) techniques. Tissue protein analysis will include standard immunohistochemistry (IHC) and/or multiplex immunofluorescence assays (*i.e.* Akoya Biosciences). Stained tissue sections will be quantified by whole-slide tissue scanning systems (*i.e.* Vectra Polaris, PerkinElmer) and further analyzed with an image analysis software (*i.e.* HALO, Indica Labs).

All multi-omic analysis will be assessed longitudinal for intra/inter tumor heterogeneity and further correlated with therapy response and clinical outcome. Moreover, samples will be compared between the 2 different patient groups (control arm vs. treatment arm).

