### 8.7.6 Liquid biopsies

Study specific interventions include biobanking of liquid biopsies (serum, plasma, PBMCs) on day -21 to -1, 7, 14, 28, 42, before surgery and at the EOSV. Blood samples are tried to be collected during routine blood drawing. Biobanking material (blood and tissue) will be used for genomic, transcriptomic, epigenomic and/or proteomic investigations/correlations with therapy response and clinical outcome.

Analysis of longitudinal liquid biopsies will be analyzed according to the above-mentioned tumor tissue biopsies.

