#### 11.4.5 Baseline parameters and concomitant medications

Baseline parameters, such as age, sex, tumor stage, etc. will be included as confounder into the analyses of secondary objectives, if appropriate. For safety and tolerability analyses, these parameters will not be considered.

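### Section 11.4.3 names only T-tests or Mann-Whitney-U tests for continuous secondary outcomes, so the planned longitudinal markers have no method that uses each patient's own screening value

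*Protocol*

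**What the plan says.** Section 11.4.3 of the protocol chooses the test by type of outcome: "Statistical analysis of secondary objectives, especially between control and treatment arm will be performed according the nature of the outcome parameter". For continuous outcomes it says "continuous variables will be compared by T-tests" (on the log2 scale) "or by Mann-Whitney-U tests and censored survival outcomes by Cox-regression analysis". It adds that "Potential confounders will be considered in corresponding statistical models". Section 11.4.5 gives examples of such variables: "Baseline parameters, such as age, sex, tumor stage, etc. will be included as confounder into the analyses of secondary objectives, if appropriate". The measured marker's own pretreatment value is not among the examples.

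The sampling is serial:

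- **Tumour tissue:** screening (day -21 to -1), day 14 and day 28, plus the resected specimen (section 8.7.5).
- **Blood:** seven time points (section 8.7.6).
- **Stool:** four visits (Table 4).

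On tissue, section 8.7.5 states: "All multi-omic analysis will be assessed longitudinal for intra/inter tumor heterogeneity and further correlated with therapy response and clinical outcome". It then adds, as a separate aim, a comparison of the samples between the two arms. On blood, section 8.7.6 states: "Analysis of longitudinal liquid biopsies will be analyzed according to the above-mentioned tumor tissue biopsies". Section 8.7.7 also describes the stool data as longitudinal and plans a between-arm comparison of them.

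**The concern.** The methods section and the sampling sections do not match. The test is selected by whether an outcome is nominal, continuous or censored, not by whether it is measured once or repeatedly in the same patient. The Mann-Whitney-U test is for independent samples. The T-test is named without saying whether it is paired. Nothing named in 11.4.3 or 11.4.5 uses the link between a patient's samples.

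What is at stake is efficiency in a trial of 80 patients. The day 14 and day 28 biopsies are taken specifically for the study, and much of their value is that each can be read against the same patient's screening sample. A method that sets this aside gives up precision that the trial has already paid for, in analyses that must also pass a multiplicity correction.

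**Working it through.** The protocol gives no power figure for the secondary outcomes, so there is none to reproduce. The check compares the named tests with baseline-adjusted or paired ones.

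**Inputs.** From the protocol: 50 treatment and 30 control patients, and significance at 0.05. Assumed: two-sided tests, normal data on the log2 scale with SD 1, and a within-patient correlation rho of 0.5 (range 0.3 to 0.7). The protocol gives no correlation.

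**1. Is a single-visit T-test between arms valid?** Yes. In simulation its false-positive rate was 0.047 to 0.054 at every rho from 0 to 0.9.

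**2. What does it cost in power?** With the screening value as covariate, the residual SD falls from 1 to sqrt(1 - rho²). The standard error of the arm difference per unit SD is sqrt(1/30 + 1/50) = 0.231. If the difference is set so that ANCOVA has 80% power, its standardised size is 1.96 + 0.84 = 2.80. The T-test sees 2.80 × sqrt(1 - rho²), so its approximate power is Φ(2.80 × sqrt(1 - rho²) - 1.96).

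| rho | sqrt(1 - rho²) | T-test, formula | T-test, simulated | ANCOVA, simulated |
|---|---|---|---|---|
| 0.3 | 0.954 | 76% | 78% | 80% |
| 0.5 | 0.866 | 68% | 67% | 79% |
| 0.7 | 0.714 | 52% | 52% | 80% |

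At a fixed difference of 0.65 SD, the T-test has 80% power and ANCOVA 84%, 90% and 98% at rho 0.3, 0.5 and 0.7.

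**3. What if change from screening is tested without pairing (n = 50)?** The unpaired T-test works with a standard error of sqrt(2/50) = 0.200. The true standard error of the mean change is sqrt(2(1 - rho)/50) = 0.167, 0.141 and 0.110 at rho 0.3, 0.5 and 0.7. The test is therefore too conservative.

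| rho | False-positive rate, unpaired | Power at a 0.4 SD shift, unpaired | Same, paired |
|---|---|---|---|
| 0.3 | 1.6 to 2.0% | 51% | 65% |
| 0.5 | 0.4% | about 50% | 79% |
| 0.7 | 0.0% | 51% | 95% |

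A separate simulation set the shift at each rho so that the paired T-test had about 80% power (81%, 80%, 78%). The unpaired T-test then had 69%, 52% and 24%, and the Mann-Whitney-U test 66%, 48% and 22%. At rho 0.5 their false-positive rates were 0.7% and 0.9%.

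**The case against.** The strongest reply is that 11.4.3 is one general sentence about all continuous secondary outcomes, aimed mainly at the comparison of arms. There a T-test at one visit, or a Mann-Whitney-U test, is legitimate. The word T-test does not exclude the paired form. Models with confounders are allowed, and the list in 11.4.5 is open, so a screening value could be added. No before-and-after hypothesis test is spelled out; the stated objective is to correlate marker patterns with response and outcome. Finer modelling is commonly left to an SAP, which may exist. At rho 0.3 the gain from ANCOVA is only about two percentage points.

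Most of this stands, and it limits the point. What it does not remove is that longitudinal analysis is promised as an aim separate from the between-arm comparison, while the only tests named for continuous outcomes make no stated use of the repeated sampling. The examples of adjustment variables in 11.4.5 do not model within-patient correlation, and they apply only where thought appropriate. Nor is the point just about missing detail: a specific test is named, and a better one is available from data already collected.

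A reader might go further and infer that the plan inflates false positives. That would follow if all visits were pooled as independent observations. In simulation the nominal 5% would become about 13 to 21% with three samples per patient and 25 to 39% with seven, over rho 0.3 to 0.7. The Holm or Benjamini-Hochberg step would not repair such p-values. But nothing in the protocol says visits will be pooled. A reader might also infer that serial analyses make up most of the secondary objectives. Section 6.2 lists six, and only two of them, on liquid and tumour biopsies, specify serial sampling.

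**Conclusion.** The point holds as a missed improvement with a mismatch in wording, not as an invalid analysis. Read literally, the named tests give a valid comparison of arms at one visit with less power than the data allow: about 67% against 79% at rho 0.5, nearly equal at rho 0.3, and 52% against 80% at rho 0.7. If change within patients is tested without pairing, power at rho 0.5 is about 50% against about 80%, and the test rejects a true null less than 1% of the time.

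These sizes rest on an assumed correlation, equal at all visits, and on normal data with full arms of 50 and 30. The claim that the protocol prescribes independent-sample T-tests for serial samples is not supported. Only secondary analyses are affected; the primary safety conclusion is untouched.

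**What to change.** In section 11.4.3, add a rule for continuous markers that are sampled serially:

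- **Between arms, one visit:** ANCOVA on the log2 value, with the same marker's screening value (day -21 to -1) as covariate.
- **Between arms, several visits together:** a mixed model with a patient effect and the same screening covariate.
- **Change within patients:** a paired T-test or Wilcoxon signed-rank test.
- **Unit of inference:** the patient, so that visits, tumour regions or cells from one patient are never counted as separate patients. This rules out the pooling risk.
- **Outcomes measured once per patient:** keep T-tests and Mann-Whitney-U tests.

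The resulting p-values go into the multiplicity correction already stated. The log2 scale may not suit every assay, so the rule should allow another scale where needed. The marker-response correlations need the same patient-level principle, but the between-arm model does not replace them.

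The cost is a wording change and slightly more modelling, with no extra patients, visits or samples. Missing screening values must be handled; section 11.4.1 already provides imputation by predictive mean matching for secondary data where appropriate, so a cross-reference should do.

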#### 11.4.4 Safety and tolerability endpoints

The safety analysis will be performed in all participants who have received at least 1 dose of study treatment. Descriptive statistics of safety will be presented using latest NCI CTCAE by treatment arm. Adverse events, treatment-related AEs, SAEs and treatment-related SAEs will be tabulated using worst grade per latest NCI CTCAE criteria by system organ class and preferred term. On-study lab parameters including hematology, chemistry including liver function and renal function will be summarized using worst grade per latest NCI CTCAE criteria.

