| CONCOMITANT MEDICATION                       | 
Allowed
 
N.A.
 
Not allowed
 
N.A.
                                                                                                                                                                                                                                                                                                                                                                                                                                                                                                                                                                                                                                                                               |
| EFFICACY ENDPOINTS                           | See primary and secondary objectives.                                                                                                                                                                                                                                                                                                                                                                                                                                                                                                                                                                                                                                                                                                                 |
| TOLERABILITY / SAFETY ENDPOINTS              | 
Surgical complications will be assessed and graded according to the latest "Clavien-Dindo Classification of surgical complications".
 
The latest National Cancer Institute (NCI) CTCAE will be used to assess any adverse effects of the drugs (Ipilimumab, Nivolumab) used in the presents study.
                                                                                                                                                                                                                                                                                                                                                                                                                                       |

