| PHARMACOKINETIC / PHARMACODYNAMIC ENDPOINTS  | N.A.                                                                                                                                                                                                                                                                                                                                                                                                                                                                                                                                                                                                                                                                                                                                                  |
| QUALITY OF LIFE / PHARMACOECONOMIC ENDPOINTS | Quality of life will be assessed by the latest version of the European Organization for Research and Treatment of Cancer (EORTC) Quality of Life Group (QLG) questionnaires C30 and CR29.                                                                                                                                                                                                                                                                                                                                                                                                                                                                                                                                                             |
| STATISTICAL METHODOLOGY                      | 
Primary Endpoint
 
Safety, tolerability and feasibility of standard neoadjuvant CRT with sequential ipilimumab and nivolumab following surgical resection.
                                                                                                                                                                                                                                                                                                                                                                                                                                                                                                                                                                         |

[figure not shown]

Safety and tolerability will be represented by published values of known complications of CRT following surgery (Table 1).

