**Table 1. Incidence of know complications for neoadjuvant CRT following surgical resection.**

| Complications (n=128)          | Percentage (%) | Citation |
|--------------------------------|----------------|----------|
| Any postoperative complication | 39             | [1]      |
| Any surgical complication      | 23             | [1]      |
| Reoperation                    | 7              | [1]      |

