### Null and alternative hypotheses

$H_0$ : Addition of sequential ipilimumab and nivolumab to standard neoadjuvant CRT is not safe and tolerable and/or increase surgical complication rates.

$H_1$ : Addition of sequential ipilimumab and nivolumab to standard neoadjuvant CRT is safe and tolerable and does not increase surgical complication rates.

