After end of the study the case numbers of each complication will be compared to the corresponding calculated  $CI_{low}$  and  $CI_{up}$  numbers for both groups and further rated. If in both groups the numbers are between these borders,  $H_0$  is rejected and the treatment is considered as safe and tolerable. If the case numbers are above the  $CI_{up}$  border in the treatment group,  $H_0$  will be accepted for this complication and the treatment is considered unsafe. If case numbers for a specific complication are below the corresponding  $CI_{low}$  border in the control group, a new complication percentage with confidence intervals for the treatment group will be calculated using the real case numbers in the control group and the case numbers in the treatment group reassessed. For the complication "reoperation" an assessment after every 10 patients of the treatment group will be performed and if the observed case numbers are above the calculated  $CI_{up}$  border case numbers, the study will be terminated (Table 3).

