## 6 STUDY OBJECTIVES

### 6.1 Primary objective

- Safety, tolerability and feasibility of sequential neoadjuvant ipilimumab and nivolumab in combination with standard neoadjuvant CRT, following surgical resection, assessed by the latest “Clavien-Dindo Classification of surgical complications” [26] (see section 9.1.2 ) and Common Terminology Criteria of Adverse Events (CTCAE) [27] (see section 9.4 ).

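### The decision rule calls the treatment safe and tolerable from post-operative complication counts alone, so CTCAE toxicity before surgery cannot change the verdict although CTCAE is part of the primary objective

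*Protocol*

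**What the plan says.** Protocol 6.1 sets the primary objective as "Safety, tolerability and feasibility of sequential neoadjuvant ipilimumab and nivolumab in combination with standard neoadjuvant CRT", assessed by Clavien-Dindo and by "Common Terminology Criteria of Adverse Events (CTCAE"). The synopsis divides the work between the two scales: Clavien-Dindo grades surgical complications, and CTCAE "will be used to assess any adverse effects of the drugs (Ipilimumab, Nivolumab"). The null hypothesis in the synopsis is that the addition of the two drugs "is not safe and tolerable and/or increase surgical complication rates", so it names general safety and tolerability separately from surgical complications.

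The rule that answers this is narrower. According to the synopsis, "Safety and tolerability will be represented by published values of known complications of CRT following surgery (Table 1"). Table 1 has three entries: any postoperative complication 39%, any surgical complication 23%, reoperation 7%. After the study the counts are compared with borders of the Table 2 kind. If both groups lie within them, the null hypothesis "is rejected and the treatment is considered as safe and tolerable". A treatment-arm count above the upper border makes the treatment unsafe for that complication. Section 11.4.2 repeats the comparison for n=50.

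CTCAE appears in the analysis only in 11.4.4: "Descriptive statistics of safety will be presented using latest NCI CTCAE by treatment arm", by worst grade, with no reference rate, threshold or link to the hypotheses. The interim rule (11.4.6, Table 3) uses reoperation only.

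**The concern.** The conclusion is wider than the data that decide it. Two scales are named in the primary objective, and the one assigned to the effects of the study drugs plays no part in the verdict. The null hypothesis has two limbs. Only the surgical one is examined, but a pass is declared for both.

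Timing makes this matter. By Table 4, ipilimumab is given in week 1 and nivolumab in weeks 2, 4 and 6, while surgery is in weeks 15 to 17. Adverse events in that interval are collected and graded but are not post-operative complications. The trial could therefore report its headline result as safe and tolerable alongside a large excess of severe drug toxicity, with the plan followed to the letter.

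A second effect is possible. A patient whose toxicity prevents surgery cannot have a surgical complication. Whether this moves the verdict depends on how unoperated patients are counted, which the protocol does not say.

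**Working it through.** **1. The plan's own figures.** For a published rate p and n patients, the expected count is p × n rounded half up. The border is the exact binomial 95% limit × n, rounded the same way (11.4.7). This reproduces every border in Table 2 and all five cut-offs in Table 3. An exact two-sided one-sample test of 23% against 46% with 49 patients has power 0.921 (null 46%) or 0.927 (null 23%), consistent with the stated 0.90. The numbers are sound; the question is which data enter the rule.

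**2. The upper borders that decide the verdict, n=50.**

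| Table 1 item | p × 50 | Expected | Exact upper limit × 50 | Border | P(count ≤ border) at published rate |
|---|---|---|---|---|---|
| Reoperation, 7% | 3.5 | 4 | 9.62 | 10 | 0.999 |
| Any surgical, 23% | 11.5 | 12 | 19.08 | 19 | 0.995 |
| Any postoperative, 39% | 19.5 | 20 | 27.41 | 27 | 0.989 |

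If the nearest printed row of Table 2 (22.5%) is used for the 23% item, the border is 18.

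**3. Where CTCAE enters.** None of these counts contains a CTCAE grade. A pre-operative grade 3 or higher rate of 10% (5 of 50) or 80% (40 of 50) leaves every border and every count unchanged. As an invented illustration, 25/50 against 6/30 is a difference of 30 points with half-width 1.96 × √(0.5×0.5/50 + 0.2×0.8/30) = 1.96 × 0.1017 = 0.199, so a 95% CI of about 10 to 50. The verdict would not move.

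**4. Patients who do not reach surgery.** Suppose the true surgical complication rate is 46%, the doubling that 11.2 says can be excluded. The numbers operated are assumptions.

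| Operated | P(count ≤ 19), border fixed at n=50 | Rescaled border | P(count ≤ rescaled border) |
|---|---|---|---|
| 50 | 0.16 | 19 | 0.16 |
| 45 | 0.36 | 17 | 0.17 |
| 40 | 0.64 | 15 | 0.18 |
| 35 | 0.88 | 14 | 0.30 |

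The rescaled borders use the method of step 1. For 40 operated, 0.23 × 40 = 9.2, expected 9, exact upper limit × 40 = 15.38, border 15.

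**5. Precision of a CTCAE contrast, 50 against 30.** The half-width is 1.96 × √(pT(1−pT)/50 + pC(1−pC)/30). It is ±14 points at 10% and 10% (or 20% and 5%), ±20 at 50% and 20%, and ±23 at 50% and 50%.

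**The case against.** Several points on the other side are fair.

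- **Post-operative immune events can count.** Table 1 includes any postoperative complication, and 9.1.1 defines a complication as any departure from the usual course after surgery. A reader might infer that no immune toxicity could ever alter the verdict; the documents do not support that. What stands is limited to toxicity before surgery.
- **Toxicity is not ignored.** Section 7.1.7 allows termination when adverse events make the risk-benefit ratio unacceptable, 7.1.6 provides for withdrawal for unacceptable toxicity, and 11.4.4 tabulates events by arm. A large excess would be visible and could end the trial. None of this feeds the hypotheses or the wording of the verdict.
- **The rule might be read more widely.** Section 11.4.2 refers to any complication, and Table 2 runs generically from 5% to 40%. But expected rates are given only for the three Table 1 items, so the rule cannot be run on CTCAE events.
- **Drift towards a safe verdict is not established.** Section 11.4.2 states n=50, and 7.1.6 keeps later drop-outs in the sample size, which points to a fixed border. Section 11.4.1 excludes patients with missing data for a side effect, and the Table 3 borders scale with n, which points the other way. The size depends on the choice, as step 4 shows.
- **Descriptive toxicity reporting is normal in a phase II trial without formal sizing.** Agreed. The fault is the formal safe-and-tolerable verdict reached without it.
- **A between-arm CTCAE comparison is not symmetric as scheduled.** In Table 4 the visits at weeks 9 and 12 are for the treatment arm only, and the trial is open-label. This shapes the fix.

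**Conclusion.** The mismatch holds. The objective and the null hypothesis cover general safety and tolerability, but the rule decides them from post-operative counts alone. Pre-operative CTCAE toxicity of any frequency leaves the verdict unchanged. This is not a detail left to a statistical analysis plan, because the protocol itself fixes the hypotheses, the rule and the words of the conclusion.

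The drift caused by patients who miss surgery is conditional. At a true 46% rate with 40 operated, the pass probability is 0.64 if unoperated patients count as event-free against the fixed n=50 border, and 0.18 if the border is rescaled. A reader might infer a built-in bias towards safety, but the protocol does not say which count applies, so only the ambiguity is established.

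The point should be corrected because it affects the headline conclusion. It does not show that the treatment is unsafe, or that toxicity would go unrecorded.

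**What to change.** 1. In the synopsis hypotheses, the synopsis decision rule and 11.4.2, limit the verdict to no increase in post-operative or surgical complications beyond the published rates. Make no safe-and-tolerable claim from this rule alone. Simply citing a toxicity table beside such a claim would not be enough, because citation is not a criterion.
2. State that the final borders are calculated for the number of patients operated. This concerns the final verdict only; the termination rule in Table 3 is not part of this change.
3. Beside the verdict, report the proportion with at least one CTCAE grade 3 or higher event in each arm with 95% CI, and the treatment-minus-control difference with 95% CI. Use all patients who started CRT, since the 11.4.4 set of patients with at least one dose of study treatment is unclear for controls. Use events from the adverse-event visits common to both arms, leaving out weeks 9 and 12, with a sensitivity analysis that includes them.

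The cost is revised wording and one summary from data already collected. The downside is a narrower claim and an imprecise difference, about ±14 to ±23 points depending on the rates, in an open-label trial.

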### 9.2.2 Definition of adverse events

An adverse event (AE) is defined as any new untoward medical occurrence or worsening of a preexisting medical condition in a clinical investigation participant administered study drug and that does not necessarily have a causal relationship with this treatment. An AE can therefore be any unfavorable and unintended sign (such as an abnormal laboratory finding), symptom, or disease temporally associated with the use of investigational product, whether or not considered related to the investigational product.

A **non-serious adverse event** is an AE not classified as serious.

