## **9.5 Relationship to study drug**

For all AEs, the Investigator will assess the causal relationship between the study drug and the AE using his/her clinical expertise and judgment according to the following algorithm that best fits the circumstances of the AE:

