### Other Safety Considerations

Any significant worsening noted during interim or final physical examinations, electrocardiograms, X-rays, and any other potential safety assessments, whether or not these procedures are required by the protocol, should also be recorded as a non-serious or serious AE, as appropriate, and reported accordingly.

A special section is designated to adverse events in the eCRF. The following details must thereby be entered:

- Type of adverse event
- Start (date and time)
- End (date and time)
- Severity (Grad 1-5)
- Serious (no / yes)
- Unexpected (no / yes)
- Outcome (resolved, resolving, not resolved, resolved with sequelae, unknown, fatal)
- Relation to study drug (Related / Not related)

Adverse events are to be documented in the eCRF in accordance with the above-mentioned criteria.

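### AE causality is recorded only against the study drug, so on the term's main usage the control column of the treatment-related tables is zero by construction, and no event can be attributed to CRT

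*Protocol*

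**What the plan says.** Section 11.4.4 sets out the safety tables: "Descriptive statistics of safety will be presented using latest NCI CTCAE by treatment arm", and then "Adverse events, treatment-related AEs, SAEs and treatment-related SAEs will be tabulated using worst grade per latest NCI CTCAE criteria". The population is given as follows: "The safety analysis will be performed in all participants who have received at least 1 dose of study treatment". Neither *treatment-related* nor *study treatment* is defined there.

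The causality input comes from elsewhere. Section 9.5 states: "For all AEs, the Investigator will assess the causal relationship between the study drug and the AE using his/her clinical expertise". The eCRF list in section 9.6 (Other Safety Considerations) has a single attribution item, "Relation to study drug (Related / Not related". The list has no item for capecitabine, radiotherapy or surgery.

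Under section 11.1, the control set is made up of patients who received neoadjuvant CRT, without the two checkpoint inhibitors.

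**The concern.** A table of treatment-related events by randomised arm invites a comparison. If relatedness can only mean related to ipilimumab or nivolumab, no control patient can ever contribute an event, however well causality is judged. The control column then reflects how the field is defined and says nothing about tolerability.

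This matters because CTCAE-graded toxicity is part of the primary objective (section 6.1). The published reference rates in Table 1 cover only three postoperative or surgical outcomes, so the concurrent control arm is the only comparator the protocol offers for CTCAE events. A later SAP could redefine the tables, but it could not recover an attribution to CRT that was never collected.

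**Working it through.** The protocol states no figure on this point, so the check is mainly a comparison of its sections.

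**1. What study drug means.**
- Ipilimumab and nivolumab only: section 9.2.1, on the risks of the study drug, covers just these two. The synopsis says CTCAE "will be used to assess any adverse effects of the drugs (Ipilimumab, Nivolumab"). Section 8.2.2 lists capecitabine separately as standard of care. The Table 4 footnote labels the treatment arm as standard of care plus IMP.
- Wider use: section 8.2 places capecitabine under study medications, and one exclusion criterion in 7.1.3 speaks of study drugs of the chemotherapy regimen.

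The narrow meaning dominates, but usage is not uniform.

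**2. Consequence under each meaning.**
- Narrow: controls have no exposure, so related events are 0 of 30 under any causality rule.
- Wide: controls can have capecitabine-related events. Radiotherapy toxicity still has no place, and one yes/no answer pools capecitabine with the checkpoint inhibitors.
- Under both, CRT attribution cannot be separated from immunotherapy attribution. Timing does not help: CRT runs over weeks 1 to 5 in Table 4, with ipilimumab at week 1 and nivolumab at weeks 2, 4 and 6, so ipilimumab and two of the three nivolumab doses overlap CRT.

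**3. Direction of error in the treatment arm.**
- Section 9.5 counts an event as related only if nothing else explains it, and as not related if another therapy given to the patient can explain it. Taken literally, an event that CRT explains is not related.
- Section 9.6 asks only for a reasonable causal link, meaning evidence that suggests one. It does not require other causes to be ruled out, so the same event may be called related.

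The two rules give different answers for the same event, so the direction is undetermined.

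**4. Illustration (all rates assumed; narrow meaning).** Arm sizes of 50 and 30 come from the synopsis. Let r be a CRT toxicity rate that is equal in both arms, and s the share of those events called related in the treatment arm. Expected related count, treatment arm = 50 × r × s. True control cases = 30 × r; control cases shown as related = 0.

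| r | True control cases | Shown, s = 0 | Shown, s = 0.5 | Shown, s = 1 |
|---|---|---|---|---|
| 10% | 3 | 0/50 vs 0/30 | 2.5/50 vs 0/30 | 5/50 vs 0/30 |
| 20% | 6 | 0/50 vs 0/30 | 5/50 vs 0/30 | 10/50 vs 0/30 |
| 30% | 9 | 0/50 vs 0/30 | 7.5/50 vs 0/30 | 15/50 vs 0/30 |
| 40% | 12 | 0/50 vs 0/30 | 10/50 vs 0/30 | 20/50 vs 0/30 |

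Fisher's exact p for s = 1 is 0.15, 0.011, 0.0006 and <0.0001. For s = 0.5, with 2.5 and 7.5 taken as 2 and 8, it is 0.53, 0.15, 0.022 and 0.011. The plan runs no such test; the values only show how the rows could look to a reader when the true difference is nil.

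Read as data, 0/30 would have an exact 95% upper limit of 1 − 0.025^(1/30) = 0.116, or 11.6%. That limit would be meaningless, because the zero is not observed.

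The s = 0 column is section 9.5 applied literally. The other two are possible under the section 9.6 wording.

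**The case against.** Four points can be made for the plan.

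- **All-cause tables exist.** Section 11.4.4 also tabulates all AEs and all SAEs by worst grade. Between randomised arms these measure added toxicity without any attribution. This stands, and it limits the point. A reader might infer that added toxicity cannot be assessed at all; that is not so.
- **Nothing is decided on relatedness.** The tables are descriptive. The primary rule compares complication counts with Table 2 (section 11.4.2), and stopping uses reoperation counts (section 11.4.6). This also stands.
- **The zero is an inference.** The wide meaning of study drug is possible, and table definitions are often left to an SAP. This stands in part: the zero depends on the narrow meaning. The missing CRT attribution does not, and it is a gap in data collection. Section 9.6 does have the SAE narrative specify a link to study conditions or procedures for SAEs judged unrelated to study drug, but that is free text for SAEs only.
- **Section 9.5 already sends CRT-explained events to the not-related category.** A reader might infer that the tables charge CRT toxicity to immunotherapy. The documents do not support that as a general statement. Under 9.5 the risk is the reverse, since real immune toxicity that resembles CRT toxicity could be missed. Over-attribution arises only under the looser 9.6 wording.

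A reader might also infer, from an AE definition that refers to an occurrence "in a clinical investigation participant administered study drug", that control-arm events go uncollected. Section 9.6 starts collection of SAEs and non-serious AEs at written consent, whatever their relatedness, and the AE row of Table 4 is marked from day 0 to the end-of-study visit. Only visits 9 and 10 are restricted to the treatment arm.

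**Conclusion.** The point holds in a limited form. On the protocol's main use of study drug, the treatment-related AE and SAE rows have a fixed zero for the 30 controls and are not a valid between-arm comparison. On any use of the term, the data cannot attribute an event to CRT separately from the checkpoint inhibitors. The direction of misattribution within the treatment arm is open, because sections 9.5 and 9.6 conflict.

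The size cannot be derived from the protocol. The illustrated range, from 0/50 to 20/50 against 0/30 with no true difference, rests wholly on assumed event rates and attribution shares. The consequence is confined to descriptive tables and does not reach the primary decision or the stopping rule. It is worth correcting because it bears on the CTCAE part of the primary objective and is cheap to correct.

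**What to change.** - **Sections 9.5 and 9.6 (eCRF list):** record relatedness separately to (a) CRT/capecitabine, answered in both arms, and (b) ipilimumab/nivolumab.
- **Sections 9.5 and 9.6 (definitions):** reconcile them so that one rule for relatedness applies throughout.
- **Section 11.4.4 (tables):** state that the between-arm comparison rests on the all-cause AE and SAE tables. Define treatment-related as related to any protocol treatment, CRT included, and show immunotherapy-related events for the treatment arm only.
- **Section 11.4.4 (population):** state that study treatment in the safety set includes CRT, so that controls are counted.
- **Unchanged:** keep AE collection from written consent in both arms. Starting it at the first day of CRT would shorten the existing window.

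The cost is one extra eCRF entry per AE, with slightly more work for investigators, and wording changes in three sections.
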